### Goal of the Study

Honey contains antibacterial components that can help treat wound infections, relieve pain, and promote circulation, which all contribute to the healing process. Studies on the use of honey in wound care have primarily been conducted on superficial wounds as well as diabetic ulcers and burns. Previous clinical trials on the use of honey in wound care looked at applying honey to wounds after excision of pilonidal cysts [19]. Research by Rai et al [20] in 2023, which included a randomized controlled trial, compared the use of honey and Edinburgh University’s solution of lime in necrotizing fasciitis wounds. Research by Dubhashi and Sindwani [21] in 2015 looked at the comparative use of honey and phenytoin in chronic wounds. In 2017, Esser [22] examined the use of leptospermum honey on wound healing on the skin of premature newborns admitted to the neonatal intensive care unit. In 2007, Güneş and Eşer [23] compared honey dressings and ethoxy-diamino acridine plus nitrofurazone dressings in patients with decubitus ulcers and assessed healing with the pressure ulcer scale for healing. Wahdini et al [24] reported the use of Madu Nusantara, an Indonesian honey, as a wound dressing for extensive diabetic ulcers in 1 patient with a history of uncontrolled type 2 diabetes mellitus, with good results. Saputri et al [25] from [name] Hospital also reported a case of using Madu Nusantara as a wound dressing in a patient with a submandibular abscess with necrotizing fasciitis. Notably, clinical trials assessing the use of honey on patients with deep neck abscesses have never been conducted before. The mechanistic action of honey in wound healing has been widely hypothesized; however, no one has evaluated its effect clinically, systemically, or on the proinflammatory cytokines and growth factors that play a role in each phase of wound healing.

Thus, this study will conduct a clinical trial of honey as one of the modalities in the treatment of deep neck abscess wounds. Honey is expected to become an alternative dressing material in the treatment of deep neck abscess wounds due to its effectiveness, safety, availability, and affordability compared to standard dressings. Furthermore, honey is readily obtainable at an affordable price; therefore, if the results of wound care using honey are positive, this work will significantly reduce the burden of care on patients, doctors, and hospitals.

## Methods

### Study Design

This study is an experimental, quantitative study to determine the effectiveness of honey in treating deep neck abscess wounds. The research design used was a single-blind randomized controlled trial, and the intervention was given randomly to the research participants. This protocol follows the SPIRIT (Standard Protocol Items: Recommendations for Interventional Trials) 2013 guidelines [26].

### Recruitment of Participants

This study investigated wound care strategies for patients with deep neck abscesses. The research design used a single-blind randomized controlled trial comparing honey dressings with standard dressings (Prontosan irrigation solution). The study population included patients treated at [name], Yogyakarta. Patient recruitment was conducted from the date of ethical clearance issuance until the required sample size was achieved. Before enrolment, all patients provided written informed consent after being fully informed of the study objectives, procedures, potential risks, and benefits. The study protocol was approved by the Medical and Health Research Ethics Committee, Faculty of Medicine, Public Health and Nursing, Universitas Gadjah Mada, [name] Hospital (KE/FK/0668/EC/2024), ensuring compliance with national and international ethical standards. The inclusion criteria included patients aged older than 18 years with or without comorbidities, except for malignant diseases. The exclusion criteria excluded patients who refused the intervention, underwent vacuum-assisted closure, or had incomplete medical records. Severe allergic reactions to dressings were considered withdrawal criteria. Our findings contribute to the optimization of wound care practices for deep neck abscesses, aiming for improved outcomes and cost-effectiveness. Our investigation was held at the ORL-HNS Department in [name] Hospital.

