**Methods:**

This is a single-blind randomized controlled trial. Randomization will be done through simple random sampling. The population and sample of the study include all patients with deep neck abscesses treated at [name] Hospital, which is equipped with board-certified otorhinolaryngologists. Patients with deep neck abscesses who were given ethical clearance and meet the inclusion criteria were recruited as study participants until the sample size was reached. There are 18 participants in each group. Participants in the intervention group received standard dressings in addition to honey dressings, whereas those in the control group received standard dressings alone. Proinflammatory cytokines and growth factors, wound size, Bates-Jensen Wound Assessment Tools scoring, and quantitative bacterial colony identification will be all evaluated and assessed. The gathered data will be documented and subjected to statistical analysis.

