### Randomization

In the study we conducted, participants were assigned to the control and intervention groups using a comprehensive randomization technique. The distribution was carried out by concealing opaque envelopes with numbered slips ranging from 1 to 36. These slips were arranged in a box, and the sequence was chosen using the Microsoft Excel random generator. Importantly, the researchers remained blind to the randomization findings throughout the process.

The participants were then assigned to either the control group (standard dressing) or the intervention group (standard dressing plus Indonesian Nusantara honey). The resident doctor was responsible for administering the dressing and obtaining detailed randomization instructions.

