### Intervention Procedure

Both the control and intervention groups received wound care following the standard operating procedure established by the Laryngopharyngology Division, ORL-HNS Department, [name] Hospital. This protocol includes wound debridement, saline irrigation, application of gauze rolls, and administration of Prontosan. Necrotic tissue was removed, and the wound was disinfected using sodium chloride before a gauze roll soaked with antibiotic ointment was inserted to serve as drainage. Dressing frequency was determined based on the volume of pus produced—daily dressing was performed until pus production decreased to less than 5 cc, at which point dressings were changed every 3 days, eventually decreasing to once a week when no pus was observed.

In the intervention group, the standard protocol was followed with an additional intervention using Nusantara honey. A 120-cm gauze roll was immersed in 12 cc of Nusantara honey for approximately 1 minute, allowing full absorption before being applied to the wound and covered with sterile gauze. Prontosan gel was used when pus was no longer present to stimulate granulation tissue formation until the wound base reached the surface. Wounds were generally left to heal by secondary intention, unless primary closure or reconstruction was necessary due to extensive tissue loss.

Monitoring of adverse events was conducted directly by the principal investigator and otorhinolaryngology residents during each wound dressing session. If the honey dressing failed to achieve adequate wound healing outcomes, a swab was taken from the wound base for repeat sensitivity culture. The wound care protocol was then reverted to the standard dressing procedure used at [name] Hospital, followed by further management based on the patient’s condition, including the treatment of any comorbidities that might hinder the healing process. The antibiotic protocol applied to both the control and intervention groups included ceftriaxone and metronidazole upon initial presentation, with adjustments made according to the culture results when available. In cases of infection escalation, antibiotics were modified following the hospital’s infection control guidelines. The average wound healing time was 7 days, although some cases required up to a month or additional surgical interventions, such as grafting.

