### Outcomes

In this study, a research assistant collected samples after completing wound dressing and storing the dressing materials. Measurements were taken on the first, seventh, and fourteenth days for BWAT assessments, as well as the first and fourteenth days for bacterial colony identification from wound bed swabs and cytokine and growth factor expression analysis from tissue samples. The resident doctor was accountable for the dressing and performed pus aspiration and tissue sampling. All information was meticulously documented on an authorized form. Wound measures included length, width, and depth, with data based on the largest width and length. Wound depth was measured using a probe perpendicular to the wound’s length and width. BWATs were evaluated by an uninformed research assistant. Bacterial culture findings and the number of bacterial colonies were used as evidence of infection improvement. Swabs from the wound bed were delivered to the microbiology lab. Tissue samples were sent to the Anatomical Pathology lab for immunopathological examination of wound healing, including quantification of IL-1, TNF-α, and VEGF expression. Tissue samples were collected using nasopharyngeal biopsy forceps, and the preserved tissue was sent out for analysis. Additionally, laboratory examinations, radiographs, and patient comorbid factors were documented for analysis in the case report form.

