### Statistical Analyses

The Shapiro-Wilk test will be used to assess the normality of continuous data because the sample size is less than 50. For comparison of wound healing outcomes between the honey dressing and standard dressing groups at each time point (days 1, 7, and 14), either an independent *t* test or Mann-Whitney U test will be used, depending on data distribution. To analyze the overall effect of treatment over time and assess the interaction between treatment group and time, a generalized estimating equation analysis will be performed. A *P* value of <.05 will be considered statistically significant. All data will be analyzed using SPSS software version 25.0 (IBM Corporation) and presented in tables summarizing the changes on days 1, 7, and 14 (Figure 2).

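### Comorbidity is admitted, acknowledged as a hindrance to healing and recorded for analysis, but neither the allocation nor the stated comparisons use it; one prespecified covariate would close the gap

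*Protocol article*

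**What the plan says.** Four parts of the protocol article bear on this.

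- **Who enters** (Recruitment of Participants): "The inclusion criteria included patients aged older than 18 years with or without comorbidities, except for malignant diseases".
- **How they are allocated** (Abstract, Methods): "Randomization will be done through simple random sampling", and "There are 18 participants in each group". The Randomization section adds: "The distribution was carried out by concealing opaque envelopes with numbered slips ranging from 1 to 36". No stratification factor is named in either place.
- **What is believed and recorded.** Intervention Procedure, describing care when honey does not work well enough, speaks of further management "including the treatment of any comorbidities that might hinder the healing process". Outcomes says: "laboratory examinations, radiographs, and patient comorbid factors were documented for analysis in the case report form". Footnote d of Table 1 lists fasting glucose and hemoglobin A1c among the laboratory tests.
- **What is compared** (Statistical Analyses): a t test or Mann-Whitney U test between arms at days 1, 7 and 14, and a GEE whose stated purpose is "To analyze the overall effect of treatment over time and assess the interaction between treatment group and time". No covariate is mentioned.

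The Blinding section says allocation is disclosed only after the final database lock. The Results section says all 36 participants are enrolled and analysis is under way.

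**The concern.** A patient characteristic that the article itself links to slower healing is let in by design and written into the case report form for analysis. It is then left to chance both in the allocation and in the comparison. The stated two-sample tests cannot take a covariate, and the stated purpose of the GEE involves only treatment and time.

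This differs from adjusting for day-1 wound size. Two wounds of equal size on day 1 may close at different rates if one patient has a comorbidity that impairs healing. In a trial of 36, the arms may differ noticeably on such a factor. The estimate from this one trial would then carry part of the comorbidity effect, for or against honey. Even with balanced arms, the variation due to comorbidity stays in the error term and costs precision.

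**Working it through.** **1. The plan's own figure.** Inputs from Sample Size: control mean 0.266 cm, SD 1.183 cm, honey mean 1.433 cm, Zα = 1.64, Zβ = 1.28. The difference is 1.433 − 0.266 = 1.167 cm.

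n per arm = 2 × [1.183 × (1.64 + 1.28) / 1.167]² = 17.5, rounded up to 18. The stated size reproduces. (Zα = 1.64 is a one-sided value. That is a separate matter; the power figures below use a two-sided 5% t test.)

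**2. Chance of an imbalance.** The documents give no comorbidity prevalence. I assume one third to one half, with 18 per arm, and take the number affected in each arm as Binomial(18, p).

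| Prevalence p | Gap of 4 or more patients | Gap of 6 or more |
|---|---|---|
| 1/3 | 21.5% | 5.0% |
| 0.4 | 23.3% | 6.0% |
| 1/2 | 24.3% | 6.5% |

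These are two-directional, so half of each figure is an imbalance that favours honey. If the total number affected, K, is fixed instead, the result depends on whether K is odd or even, because the gap must have the same parity as K. For K = 12 to 18 of 36, the chance of a gap of 4 or more runs from 16.4% (K = 13) to 31.8% (K = 18), and of 6 or more from 3.5% to 9.4%. The binomial figures average over this and are the fairer summary.

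**3. Shift in the estimate.** I assume the comorbidity slows closure by d = 0.5 to 1.0 cm (not in the documents). Shift = d × gap / 18.

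- Gap of 4: 0.5 × 4/18 = 0.11 cm to 1.0 × 4/18 = 0.22 cm, or 10% to 19% of 1.167 cm.
- Gap of 6: 0.5 × 6/18 = 0.17 cm to 1.0 × 6/18 = 0.33 cm, or 14% to 29%.

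The planned standard error is 1.183 × √(2/18) = 0.394 cm, so the shifts are roughly 0.3 to 0.8 standard errors.

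**4. Error rates of the crude test.** A simulation with no honey effect, prevalence 40% and a comorbidity effect of 0.5 to 1.0 SD gave a two-sided type I error of 5.0% to 5.1% averaged over randomizations. Given a particular imbalance, the false-positive rate in favour of honey (nominal 2.5%) was 4.6% to 6.3% with 4 fewer affected patients on honey, and 6.3% to 11.7% with 6 fewer. With equal numbers affected it was below nominal, 1.5% to 2.2%.

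**5. What adjustment buys.** At p = 1/2, the share of variance removed is p(1 − p)d² / 1.183² = 0.25d² / 1.3995. This is 4.5% for d = 0.5 and 17.9% for d = 1.0, and the residual SD falls from 1.183 to 1.156 or 1.072 cm. Two-sided t-test power at 18 per arm, averaged over chance imbalance and with one degree of freedom spent:

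| Analysis | Comorbidity effect | Power |
|---|---|---|
| Crude | any (total SD held at 1.183) | 82.0% |
| Adjusted | none | 80.8% |
| Adjusted | 0.5 cm | 82.5% |
| Adjusted | 1.0 cm | 87.7% |

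**The case against.** The strongest reply is that an unadjusted comparison in a randomized trial is valid. Chance imbalance is part of the sampling error the test already allows for, and step 4 confirms this. That stands. A reader might infer that the planned tests have an inflated type I error, or that comorbidity alone could account for the planned honey effect. Neither is supported: the average error rate is about 5%, and under the assumed range an imbalance explains only about 10% to 29% of the planned difference. Nor is an imbalance likely; more than three quarters of randomizations would show no gap of 4 patients.

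A reader might also infer that allocation is unrestricted. The phrase simple random sampling points that way, but 36 slips and 18 per group fit fixed totals. Tossing a coin for each of 36 patients would give exactly 18/18 only 13% of the time. What the article supports is that allocation is not stratified by comorbidity.

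It can further be said that the article is condensed and that an unseen analysis plan may name covariates. It may, and the article does not say that the GEE excludes them. The point therefore rests on what is printed: one section records comorbidity for analysis, and the section that sets out the analysis gives it no role. Finally, the article does not single out diabetes, and its remark on hindered healing gives no size. So the choice of covariate is the sponsor's to justify, and the gain is uncertain.

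**Conclusion.** The concern holds as a matter of efficiency and of bias in the single trial actually run; it does not make the planned tests invalid. The mismatch between recording comorbidity for analysis and the stated comparisons is clear from the text. Its size rests on two assumptions that the documents do not supply: prevalence of one third to one half, and slowing of closure by 0.5 to 1.0 cm. Under these, roughly one trial in four or five has a gap of 4 or more affected patients, and gaps of 4 to 6 move the estimate by 0.11 to 0.33 cm in either direction. The power gain from adjusting is from about half a point to almost 6 points. Enrolment is complete, so only the analysis can still be changed. The change is worth making because it is cheap, but the adjusted model can carry the conclusion only if it is fixed before allocation is disclosed.

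**What to change.** Before allocation is disclosed, add a sentence to Statistical Analyses that names one binary day-1 comorbidity already in the case report form, with the reason for choosing it. Diabetes, from history or day-1 hemoglobin A1c or glucose, is an example. Enter it as a main effect in the GEE or linear model for wound size and BWAT, base the conclusion on the adjusted treatment effect, and keep the crude tests as supportive. Use one covariate only, given 36 patients.

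One technical point: a main effect is enough when the response is closure from day 1, or the day-7 and day-14 values. If the GEE keeps day 1 among its responses, comorbidity-by-time terms are needed too, because a term constant over time leaves the treatment-by-time contrast essentially unchanged.

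If allocation is already known to those analysing the data, report the adjusted model as a labelled sensitivity analysis. In either case, show comorbidity by arm in the baseline table.

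Cost: no new data or visits; one degree of freedom (more if time interactions are needed); and about 1 point of power (82.0% to 80.8%) if the covariate turns out not to be prognostic.

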### Measurements

Table 1 outlines the schedule for data collection. All participants who were intervened on had data collected on days 1, 7, and 14. The data comprised measurements of bacterial colony counts, wound size, Bates-Jensen Wound Assessment Tools (BWATs), proinflammatory cytokines, and growth factors. The data are intended to reflect the effects of interventions performed on wound healing in each stage.

**Table 1 table1:** Schedule for data collection.

Activity		Timeline (days)
Filling out the case report form		1, 7, and 14
Wound measurement		1, 7, and 14
Measuring BWATs^a^ (size, depth, edges, undermining, necrotic type, necrotic amount, exudate type, exudate amount, skin color, edema, induration, granulation, and epithelialization)		1, 7, and 14
Taking a wound bed swab		1 and 14
Taking wound tissue (biopsy)		1 and 14
Vital sign examination (blood pressure, respiratory rate, heart rate, temperature, SPO2^b^, and VAS^c^)		1-14 (daily)

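### The exclusion criteria have no time limit and withdrawal for dressing allergy follows treatment, so randomised patients could be removed for reasons linked to arm or outcome

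*Protocol article*

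**What the plan says.** The Recruitment of Participants section of the protocol article lists as exclusions "patients who refused the intervention, underwent vacuum-assisted closure, or had incomplete medical records". It gives no time point for any of the three. It then adds a separate rule: "Severe allergic reactions to dressings were considered withdrawal criteria". It does not say whether withdrawal means stopping the dressing, leaving follow-up or leaving the analysis.

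Other parts of the article that bear on this:

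- Consent comes first: "Before enrolment, all patients provided written informed consent" (same section).
- Allocation used "concealing opaque envelopes with numbered slips ranging from 1 to 36" (Randomization). No rule for replacing a removed participant is described.
- The resident who applies the dressing receives the randomisation instructions (Randomization). Patients are not blinded; the principal investigator and the measuring assistant are (Blinding).
- Adverse events are monitored at dressing sessions by the principal investigator and residents (Intervention Procedure).
- Outcomes are compared at each time point by t test or Mann-Whitney test, and over time by generalised estimating equations (Statistical Analyses). The article names no analysis population.
- Thirty-six participants have been enrolled and analysis is under way (Results). The participant flowchart is not available in the text.

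**The concern.** A randomised comparison is protected only if nothing that happens after allocation decides who is counted. One of the four rules certainly acts after allocation, because a reaction to a dressing needs exposure to it. The honey arm is exposed to one product more than control.

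The other three can act after allocation as worded:

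- **Vacuum-assisted closure** is a form of wound care, and the criterion has no cut-off at allocation.
- **Incomplete records**, if the term covers the trial's own forms for days 1, 7 and 14, can be judged only once follow-up has ended.
- **Refusal of the intervention** is listed separately although consent already precedes enrolment. Both arms receive the standard dressing, so after allocation the phrase would most naturally mean refusing honey.

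Patients and the dressing resident know the arm, so such removals could depend on it. With 18 per arm, one or two removals linked to healing are enough to move the result.

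**Working it through.** **Inputs** (protocol article, Sample Size): control mean closure 0.266 cm, SD 1.183 cm; expected honey mean 1.433 cm; Zα = 1.64; Zβ = 1.28; 18 per group.

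**Step 1. Reproduce the planned size and look for an allowance for losses.**

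Planned difference = 1.433 − 0.266 = 1.167 cm.

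n = 2 × [SD × (Zα + Zβ) / difference]² = 2 × [1.183 × (1.64 + 1.28) / 1.167]² = 17.52, rounded up to 18 per group.

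This matches the article. The whole 18 is used by the formula, so there is no margin for removed patients.

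**Step 2. Sort the four rules by timing.**

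| Rule | Can it be judged before allocation? | Can it be judged after, as worded? |
|---|---|---|
| Severe allergy to dressings (withdrawal) | No | Yes, only then |
| Vacuum-assisted closure (exclusion) | Yes, if already done or planned | Yes |
| Incomplete records (exclusion) | Yes, if it means the hospital chart | Yes, if it means trial records |
| Refusal of the intervention (exclusion) | Yes, as part of consent | Yes |

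**Step 3. Size of a selective removal, as an illustration.** Assumptions made here, not taken from the article: no true effect, normal data with mean 0.266 and SD 1.183 cm in both arms, 18 allocated per arm, exactly the k lowest values removed, then an unpaired t test. There were 40,000 simulated trials per case. Bias is honey minus control, in cm.

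| k removed | Honey only: bias | Honey only: two-sided rejection | Control only: bias | k from each arm: bias | k from each arm: two-sided rejection |
|---|---|---|---|---|---|
| 0 | 0.002 | 5.1% | 0.002 | 0.002 | 5.1% |
| 1 | 0.129 | 7.0% | −0.124 | 0.002 | 6.8% |
| 2 | 0.237 | 10.4% | −0.232 | 0.002 | 8.1% |
| 3 | 0.336 | 15.1% | −0.332 | 0.002 | 9.2% |

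The 0.002 in the first row is simulation noise.

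Check by hand for k = 1: the expected lowest of 18 values is about −1.89 cm. Removing it raises the mean of the other 17 by (0.266 + 1.89) / 17 = 0.127 cm, in line with the table.

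Against the planned difference, the honey-only figures are 0.129 / 1.167 = 11%, 0.237 / 1.167 = 20% and 0.336 / 1.167 = 29%.

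Removing the same number of worst healers from both arms leaves the difference unbiased. Rejection still exceeds 5%, because cutting off the lower tail makes the t test understate the variance.

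**The case against.** The strongest reply is that the article does not say what the concern fears. It puts three of the rules under exclusion and only allergy under withdrawal, so it separates the two. Consent precedes enrolment, so refusal may simply mean declining to take part. Earlier or planned vacuum-assisted closure and an incomplete chart can be screening criteria. Nowhere is it stated that an excluded or withdrawn patient leaves the analysis, and the analysis set may be defined in a fuller document. All of this stands. It is why the point is conditional. It does not remove the point, because the rules are stated without a time limit and one of them must act after allocation.

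A reader might infer several stronger claims that the article does not support:

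- **That the rules certainly favour honey.** Vacuum-assisted closure and incomplete records apply to both arms, and losses from control reverse the sign. Nothing in the article ties refusal, missing records or allergy to poor healing.
- **That the P values are invalid.** This would need actual removals linked to outcome. The text reports none.
- **That honey failures are dropped.** The article says "If the honey dressing failed to achieve adequate wound healing outcomes, a swab was taken from the wound base for repeat sensitivity culture" and that care then returned to the standard dressing. That is a change of treatment, not a removal. Such a rule can exist only in the honey arm, because controls already have the standard dressing.
- **That only treated patients are analysed.** The sentence "All participants who were intervened on had data collected on days 1, 7, and 14" describes data collection, not an analysis population.
- **That surgical closure counts as healing.** Wounds healed by secondary intention "unless primary closure or reconstruction was necessary due to extensive tissue loss". No scoring rule for these wounds is given, and the timing relative to day 14 is not stated.

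**Conclusion.** The point holds in conditional form. The eligibility and withdrawal rules are badly fixed: one necessarily acts after randomisation and three may. If any randomised patient is removed under them, the comparison is no longer fully randomised and may be biased in either direction.

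The honey-only figures (about 0.13, 0.24 or 0.34 cm, with a type I error of about 7%, 10% or 15%) are an assumed worst case, in which exactly the worst healers leave one arm. They show how sensitive a trial of 18 per arm is. They do not estimate what happened here, since neither the number removed nor its split by arm is given. If no randomised patient was removed, there is no bias from this source and only the wording needs repair.

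**What to change.** Three changes, to be made before the analysis is finalised:

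1. State that the exclusion criteria apply only to what is known before the allocation envelope is opened.
2. In the main analysis, keep all 36 randomised participants in their allocated arm, using all data collected to day 14. This includes any who later refuse, undergo vacuum-assisted closure, revert to standard dressing, are withdrawn for allergy or have incomplete records. State that withdrawal for allergy does not remove a participant from the analysis. This concerns who is counted, not how such patients are treated.
3. Show any analysis that removes such participants only as a sensitivity analysis, with the number removed, the reason and the arm.

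The cost is small. No new patients are needed. Data to day 14 would have to be retrieved for any participant already removed, and the estimate may be slightly diluted by patients who did not receive their allocated dressing throughout. If nobody was removed, the change is one of wording.
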